### Interventions

Subjects assigned to the experiment arm should receive rivaroxaban 10 mg plus clopidogrel 75 mg daily. Subjects assigned to the control arm should receive aspirin 100 mg plus clopidogrel 75 mg daily. All subjects are given medication routinely for 6 months. If subjects had never or not routinely taken clopidogrel or aspirin in the pastor taken clopidogrel 75 mg or aspirin 100 mg daily routinely less than five days before inclusion, a loading dose of clopidogrel 300–600 mg or aspirin 300–600 mg should be given within 12 h before coronary angiography.

If GIB occurs during the study, antiplatelet drugs should be discontinued, endoscopic hemostasis under the condition of stable hemodynamics, and Proton Pump Inhibitors (PPI) drug treatment are performed. Three days after hemostasis, subjects are given clopidogrel 75 mg monotherapy daily as soon as possible if the gastric injury is localized or completely hemostatic, no active bleeding relapses, and hemoglobin remains above 90 g/L after blood transfusion. Five days after hemostasis, they return to the original treatment strategy after randomization. But if there is still a small range of active or occult bleeding and the hemoglobin fluctuates above 100 g/L on different days, subjects are given low molecular weight heparin. Seven days after hemostasis, they restore to the original treatment strategy after randomization, and low molecular weight heparin was discontinued at the same time.

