## Abstract

**Background:**

Dual antiplatelet therapy (DAPT) with aspirin and a P2Y_12_ inhibitor is recommended for patients with coronary heart disease (CHD) undergoing percutaneous coronary intervention (PCI) to antithrombosis, meanwhile, increasing the risks of gastrointestinal bleeding. Rivaroxaban, a novel oral anticoagulant, combined with a P2Y_12_ receptor inhibitor reduces adverse events in patients with CHD and atrial fibrillation who underwent PCI. The effect of rivaroxaban plus P2Y_12_ inhibitor on reducing bleeding events in patients with CHD and gastrointestinal disease (GID) undergoing PCI remains unclear.

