The 2020 ESC guidelines for atrial fibrillation recommend discontinuing aspirin within 1-week and continuing (N)OAC in combination with a P2Y_12_ receptor inhibitor for up to 12 months in patients with atrial fibrillation and ACS parallel uncomplicated PCI if the risk of stent thrombosis is low or the risk of bleeding is higher than the risk of ischemia [19]. Previous studies in patients with atrial fibrillation combined with CHD, including WOEST [9], PIONEER AF-PCI [10], RE-DUAL PCI [15], ENTRUST-AF PCI [16], AUGUSTUS [17], and GEMINI-ACS-1 [11], have demonstrated that OAC in combination with an antiplatelet agent is more effective than conventional DAPT or triple OAC + DAPT. But these studies were heterogeneous with the Asian yellow population, and most of the studies enrolled Caucasians [9–11, 15–17]. Rivaroxaban is the first oral, direct Factor Xa inhibitor to receive approval from regulatory authorities for stroke prevention in patients with AF, based mainly on the Phase III results of the ROCKET AF trial [20]. Rivaroxaban has certain advantages over warfarin and other VKAs in efficacy and safety in diseases at high risk of thrombosis, including ACS. Since factor Xa plays a central role in thrombosis, inhibition of factor Xa with low-dose rivaroxaban might improve cardiovascular outcomes in patients with recent ACS. It has the advantages of rapid onset of action, predictable efficacy, no need for routine coagulation monitoring, and conventional-dose adjustment [21, 22].

Dual antithrombotic therapy with rivaroxaban 15 mg once daily plus clopidogrel is a feasible treatment strategy among patients undergoing PCI with AF in the PIONEER AF-PCI trial [10]. The study of Lin et al. [23] demonstrated that low-dose rivaroxaban 10 mg once daily was associated with equal risks of ischemic stroke, systemic embolism, or major and nonmajor clinically relevant bleeding compared with the standard dose rivaroxaban 15 mg or 20 mg once daily in Asian patients with AF. There are a lower risk of ischemia and a higher risk of bleeding in Asian populations. In this study, patients undergoing PCI without AF are receiving clopidogrel and rivaroxaban 10 mg once daily in terms of efficacy and safety.

If the results of this study are reasonable, it will provide a new strategy for the secondary prevention of CHD combined with GID undergoing PCI and more evidence for guidelines.

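### The gastrointestinal-bleed rule is internally inconsistent: its stop sentence does not address rivaroxaban, its restart steps presuppose that rivaroxaban was interrupted, and the heparin branch runs on an undefined clock

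*Protocol article*

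**What the plan says.** All the operative text is in the Interventions section of the protocol article.

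- **Regimen.** "Subjects assigned to the experiment arm should receive rivaroxaban 10 mg plus clopidogrel 75 mg daily". The control arm receives aspirin plus clopidogrel.
- **Stop step.** "If GIB occurs during the study, antiplatelet drugs should be discontinued". Endoscopic haemostasis and a proton pump inhibitor follow. Neither rivaroxaban nor anticoagulants as a class are mentioned.
- **First restart branch.** Three days after haemostasis, "subjects are given clopidogrel 75 mg monotherapy daily as soon as possible if the gastric injury is localized", or if bleeding is fully controlled, with no active relapse and a haemoglobin condition. At five days subjects go back to their randomised regimen.
- **Heparin branch.** The entry condition is "if there is still a small range of active or occult bleeding and the hemoglobin fluctuates above" 100 g/L on different days; low molecular weight heparin is then given. Its end is timed as follows: "Seven days after hemostasis, they restore to the original treatment strategy after randomization", with heparin stopped at the same moment.

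The article states rivaroxaban's drug class twice: "Rivaroxaban, a novel oral anticoagulant, combined with a P2Y_12_ receptor inhibitor" in the Abstract, and "Rivaroxaban is the first oral, direct Factor Xa inhibitor" in the Discussion.

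**The concern.** The rule governs a foreseeable event. Patients are selected for gastrointestinal disease, all receive two antithrombotic drugs, and bleeding is the primary endpoint. A rule that one clinician can read as stopping both study drugs and another as stopping only one leaves patient safety to interpretation.

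The ambiguity is also unequal between arms. Aspirin and clopidogrel are both plainly antiplatelet drugs, so the control arm has one reading at the stop step and the experimental arm has two. The trial is open-label, so the treating clinician knows which case applies.

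Different handling after a bleed could carry into later outcomes that the trial reports: BARC 3–5 bleeding, re-bleeding and MACCE. It could also affect the per-protocol set, described only as fully in line with the study, because compliance with a rule that has two readings cannot be judged consistently.

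**Working it through.** **1. Does the article treat rivaroxaban as an antiplatelet drug?** No. The Abstract calls it an oral anticoagulant and the Discussion a direct Factor Xa inhibitor. The Discussion also describes a NOAC combined with an antiplatelet agent, which keeps the two classes apart.

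**2. Apply each step to each arm.**

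| Step | Control arm | Experimental arm |
|---|---|---|
| Randomised drugs | aspirin, clopidogrel | rivaroxaban, clopidogrel |
| Stop antiplatelet drugs | both stop | clopidogrel stops; rivaroxaban not addressed |
| Day 3: clopidogrel alone | clopidogrel only | clopidogrel only, which requires rivaroxaban to be off |
| Day 5: randomised regimen | aspirin resumes | a return to the regimen, which requires rivaroxaban to have been off |

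The control column is coherent. In the experimental column, days 3 and 5 rest on an interruption that no earlier step states.

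**3. The heparin branch.** It is entered with bleeding still active or occult. Its only time point is seven days after haemostasis, and heparin has no start time of its own. Two readings are possible:

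- Haemostasis is the endoscopic procedure named earlier in the paragraph. Day 0 then exists, and the seven days can run while residual bleeding continues.
- Haemostasis is the end of bleeding. The clock cannot start while the entry condition holds, and the restart date stays open until bleeding stops.

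The text does not choose between them. This affects both arms. In the experimental arm the silence on rivaroxaban also carries into the heparin period.

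**4. How many patients could an amendment still reach?** Inputs: planned total 1020 and 6% per arm at 6 months (Sample size); 1:1 allocation (Randomization and blind); 720 recruited and 506 with complete 6-month follow-up (Trial status).

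- Check of the plan's own figure: 6% in both arms, margin 4.7%, one-sided 2.5% and 85% power give 459 per arm, so 918 in total; 918 / (1 − 0.10) = 1020, as stated. The sample size is not at issue.
- Still to enrol: 1020 − 720 = 300.
- Recruited without complete follow-up: 720 − 506 = 214, an upper bound on those still under observation.
- Total: 300 + 214 = 514; per arm 514 / 2 = 257.
- Expected BARC 2–5 bleeds in the rivaroxaban arm: 0.06 × 257 = 15.4, about 15.
- The gastrointestinal share is not given. Assuming half to all: 0.5 × 15.4 = 7.7 up to 15.4, so about 8 to 15.

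No calculation from the document gives the size of any effect on BARC 3–5 bleeding, re-bleeding, MACCE or per-protocol membership.

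**The case against.** The strongest reply is that the paragraph, read whole, shows what was meant. A step of clopidogrel alone followed by a return to the randomised regimen makes sense only if rivaroxaban was interrupted, so a careful clinician would not be misled. Much of this stands. A reader might infer from the stop sentence alone that rivaroxaban is to be continued through a bleed, and the document does not support that: it is silent on the drug at that step. The inconsistency remains, because the reader must work backwards from a later step to learn what to do at an earlier and more urgent one. The Discussion also asserts that anticoagulants do not damage the gastrointestinal tract, so the literal reading is not far-fetched.

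On the heparin branch, the reply is that haemostasis may mean the endoscopic procedure, which gives a defined day 0 with residual bleeding after it. That is a fair reading. The branch is therefore ambiguous, not proven contradictory.

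A reader might also see a conflict between the 90 and 100 g/L haemoglobin values. The text does not bear this out. The first applies after transfusion with bleeding controlled, the second with bleeding persisting; different values for different clinical states do not contradict each other.

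The rule acts only after a gastrointestinal bleed, so it cannot alter whether that bleed occurred. This stands, and it confines any statistical effect to later events and to the per-protocol set. Nothing in the article shows that the arms have in fact been handled differently.

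Finally, drug therapy and bleeding treatment are recorded at follow-up, and the DSMB receives all adverse events. These arrangements help to detect a problem but do not settle what the rule means.

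**Conclusion.** The point holds as an internal inconsistency in a stated safety rule, together with an undefined time point in its heparin branch. It is a fault in what the article prints, with drugs, days and thresholds spelled out, and not a detail left to the full protocol.

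At most about 514 patients, or 257 per arm, could still be affected. That corresponds to at most about 15 BARC 2–5 bleeds in the rivaroxaban arm, or about 8 to 15 gastrointestinal ones. The figures assume that the planning rate of 6% holds, that the remaining patients split evenly between arms, and that half to all of the bleeds are gastrointestinal. They count BARC 2–5 events only, whereas the rule is triggered by gastrointestinal bleeding without a stated grade.

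Two larger readings should be avoided. Applying 6% to all 510 patients in the arm gives 30.6 bleeds, but that includes patients who have finished and whom no amendment can reach. Nor can all 214 be taken as still in follow-up: the article says only that 506 have complete 6-month visits, so the rest may include withdrawals and losses, and those who remain have already used part of their six months.

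Distortion of BARC 3–5 bleeding, re-bleeding, MACCE or per-protocol membership is possible but cannot be sized from the document. The case for acting rests mainly on patient safety.

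**What to change.** The research team should reconcile the sentences in Interventions by amendment, with Ethics Committee approval as the Protocol amendments section provides, and inform the DSMB. The revised text should:

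- state, separately for each arm, how rivaroxaban, aspirin and clopidogrel are each handled at the stop step and at every restart step, including the heparin branch;
- define the haemostasis time point from which the heparin branch is timed.

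Which clinical rule applies is for the research team to decide; this review proposes none.

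The cost is a short amendment and a notice to staff at one centre. Sample size, margin and primary analysis are unchanged. The number of patients who can benefit falls as recruitment and follow-up proceed, so the amendment should be made promptly.

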### Schedule of assessments

After subjects provided informed consent and were enrolled in the study, the data collection is initiated. Investigators should collect information including demographic information, admitting examination, and laboratory tests.

At the follow-up visit of 30 days by telephone contact, investigators need to know about and record information as follows: (1) bleeding events, including location, time, treatment, hospitalization, and duration of hospitalization; (2) MACCE, including time of occurrence, treatment, hospitalization, and length of hospitalization; (3) reviewing concomitant medication with subjects; (4) informing subjects of the importance of compliance with study medication; (5) scheduling the next visit; (6) informing subjects and/or guardians to notify investigators of any adverse events.

At the follow-up visit of 6 months on-site, investigators should collect data as follows: (1) assessing MACCE; (2) assessing bleeding events, including location, time, treatment, hospitalization, and duration of hospitalization; (3) proceeding routine blood test and fecal occult blood test to observe whether the patient has gastrointestinal bleeding and other diseases; (4) reviewing concomitant medication with subjects. In terms of patient compliance with medication, the medication compliance of patients was judged by regular follow-up. At the follow-up visit of 30 days by telephone contact, investigators checked the amount of pills left by the subjects. During a 6-month on-site follow-up, pill boxes would be handed by subjects to check their medication compliance. At the end of the study, the physician decides whether subjects should be received which antithrombotic treatment and whether they should be received PPI and H2 receptor antagonists. Detailed schedule content is listed in Table 2. We will request consent for the review of participants’ medical records, and for the collection of blood samples to assess hematology (RBC, WBC, HGB, HCT, Plt) and fecal occult blood. Biological specimens collected from subjects will be used only for laboratory testing and will be destroyed safely when the test ends. No genetic or molecular analysis is scheduled.

**Table 2 Tab2:** Study schedule

	Enrollment (Visit 1)	1 month ± 7 days (Visit 2)	6 months ± 7 days (Visit 3)
Inclusion/exclusion criteria	√		
Informed consent	√		
Demographic data	√		
Previous history	√		
Admitting diagnosis	√		
Admitting examination and laboratory tests	√		
Information of PCI	√		
Drug therapy	√	√	√
Hematology (RBC, WBC, HGB, HCT, Plt)	√		√
FOB	√		√
Bleeding event		√	√
MACCE		√	√

*PCI* percutaneous coronary intervention, *RBC* red blood cells, *WBC* white blood cells, *HGB* hemoglobin, *HCT* hematocrit, *Plt* platelets, *FOB* fecal occult blood, *MACCE* major adverse cardiovascular and cerebrovascular event

### Endpoints

The primary endpoint of the study is Bleeding Academic Research Consortium (BARC) type 2–5 bleeding events requiring medical intervention. The secondary endpoint is a composite of MACCE including all-cause death, cardiac death, nonfatal myocardial infarction, stent thrombosis, ischemia-driven target vessel revascularization, and stroke. Other endpoints include the separate components of the MACCE and BARC 3–5 bleeding. Detailed definitions of all study endpoints are provided in Supplemental file 3.

### Adverse event reporting and harms

Adverse events (AEs), serious adverse events (SAEs), and harms from interventions will be collected and reported to CEC. Those events include bleeding events (BARC) and other serious adverse events (e.g., death, ischemia-driven target vascular revascularization, stent thrombosis, and myocardial infarction). Furthermore, the investigator will be reported to relevant regulatory bodies as needed, indicating expectedness, seriousness, severity, and causality.

### Data management and confidentiality

Case Report Form (CRF) and entering the information into an electronic database will be completed by two investigators. They are double-checked by them each other. All the CRF on paper will be stored in a locked cabinet, using the phonetic initials of the name as the code name and access to the data is only available to those who are authorized by the principal investigator. All information collected in this study will be strictly protected to ensure the privacy of participants.

### Sample size

Based on the incidence of BARC type 2–5 bleeding in the GEMINI-ACS-1 [11] trial and OPT-CAD trial, provided that the incidence of BARC type 2–5 bleeding in the experiment arm and the control arm are both 6% at 6 months. A non-inferiority margin of 4.7% was estimated and based on a one-sided type 1 error of 2.5%, power of 85%, and a 10% drop-out rate, a total of 1020 patients was needed for adequate analysis. Sample-size determination was performed with SAS version 9.3.

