**Discussion:**

The objective of this study is to evaluate the efficacy and safety of rivaroxaban plus clopidogrel versus aspirin plus clopidogrel in patients with CHD and GID undergoing PCI. We aim to explore an optimized antithrombotic strategy, which achieves the same anti-ischemic effect as standard DAPT without increasing the risk of GIB, for patients with CHD and GID undergoing PCI.

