### Statistical analysis

The analysis of the primary endpoint that BARC type 2–5 bleeding events require medical intervention for 6 months based on intention-to-treat (ITT) and per-protocol (PP) population. The ITT population is all randomized subjects. All randomized subjects without major protocol violations, subjects who did not receive the assigned treatment, or did not receive any treatment belong to the ITT population. The PP population is fully in line with the study. The study will conduct subgroup analyses of primary and secondary endpoints based on gender, age, and diabetes in the ITT population. Multiple imputation will be performed to handle missing data. The main endpoints of the ITT population are analyzed and then reanalyzed in the PP population to support the results. The analysis of the composite of MACCE is based on the ITT population. Unless otherwise stated, all hypothesis tests are carried out at a bilateral significance level of 5%. To determine whether the efficacy and safety of rivaroxaban plus clopidogrel in patients with CHD and GID are not inferior to aspirin plus clopidogrel. The difference in the incidence of endpoints between the experiment group and the control group is less than or equal to the non-inferior effect value means an invalid hypothesis (H0, P0–P1 ≤  − 4.7%). The difference in the incidence of the primary endpoint between the two groups is greater than the non-inferior effect value remains an alternative hypothesis (H1, P0–P1 >  − 4.7%). The non-inferiority test is carried out at a significance level of 0.025 on one side. Statistical analyses were performed with SAS version 9.3.

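### The 4.7-point margin is 78% of the assumed 6% bleeding rate, so a non-inferior result cannot support a claim of no increase in bleeding; below a 4.7% control rate it also contains a true doubling

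*Protocol article*

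**What the plan says.** The Sample size section sets the planning rate, "provided that the incidence of BARC type 2–5 bleeding in the experiment arm and the control arm are both 6% at 6 months", and then the margin with the error rates: "A non-inferiority margin of 4.7% was estimated and based on a one-sided type 1 error of 2.5%, power of 85" per cent. The section gives no reason for the value of the margin. It goes on to "a 10% drop-out rate, a total of 1020 patients was needed for adequate analysis".

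The Statistical analysis section puts the hypotheses on the absolute scale. The null is described as "The difference in the incidence of endpoints between the experiment group and the control group is less than or equal to the non-inferior effect value", written as P0–P1 at or below −4.7%, and "The non-inferiority test is carried out at a significance level of 0.025 on one side". The section has no relative-scale criterion and no rule for a control rate other than 6%.

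The Discussion part of the abstract describes the hoped-for regimen as one "which achieves the same anti-ischemic effect as standard DAPT without increasing the risk of GIB". The main Discussion repeats that aim.

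**The concern.** A non-inferiority test supports one statement: that an excess as large as the margin has been excluded. Here the margin is more than three quarters of the assumed event rate, while the aim is no increase in bleeding. The distance between what the test can show and what the article hopes to say is large, and nothing in the text limits the conclusion to what is shown.

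The fixed absolute scale adds to this. The rarer bleeding turns out to be, the larger the relative excess that 4.7 points represents and the easier the test is to pass. At a low enough rate the same 95% interval could meet the criterion and also show significantly more bleeding on rivaroxaban. A reader given only the word *non-inferior* would not learn that.

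**Working it through.** **Inputs.** From Sample size: 6% in both arms, margin 4.7 points, one-sided alpha 0.025, power 85%, drop-out 10%, N = 1020. From Randomization and blind: 1:1 allocation. Assumptions: P0 is control and P1 is rivaroxaban, the only reading that makes sense for a harm endpoint. The article does not name the test, so I used the upper limit of the two-sided 95% Wald interval for the risk difference.

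**1. The plan's own figure.** n per arm = 2p(1−p)(z₀.₉₇₅ + z₀.₈₅)² / margin² = 2 × 0.06 × 0.94 × 2.996² / 0.047² = 458.5, rounded up to 459. The total is 918, and 918 / 0.9 = 1020. This matches exactly.

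**2. The margin in relative terms at plan.** 4.7 / 6 = 0.78. The boundary is 6% + 4.7 = 10.7%, and 10.7 / 6 = 1.78.

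**3. When a doubling falls inside the margin.** A doubling of control rate p adds p points. It is inside the margin when p < 4.7%.

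**4. Chance of declaring non-inferiority under a true doubling.** Exact binomial enumeration, 459 per arm, success if the upper Wald limit is below 4.7 points:

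| Control rate | Risk ratio at the margin | True rates under a doubling | P(declare non-inferiority) |
|---|---|---|---|
| 6% | 1.78 | 6% vs 12% | 0.4% |
| 5% | 1.94 | 5% vs 10% | 1.9% |
| 4.7% | 2.00 | 4.7% vs 9.4% | 2.8% |
| 4% | 2.17 | 4% vs 8% | 7% |
| 3% | 2.57 | 3% vs 6% | 26% |
| 2.5% | 2.88 | 2.5% vs 5% | 44% |
| 2% | 3.35 | 2% vs 4% | 67% |

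With 510 per arm (no drop-out) the figures are similar: 0.4% at 6%, 7% at 4%, 27% at 3% and 71% at 2%. A Farrington–Manning score test moves the pass limit by at most one or two events.

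**5. What a passing result looks like at the planned rate.** With 28/459 control events (6.1%), the most that passes is 34/459 (7.4%). The risk ratio is 1.21, 95% limits 0.75 to 1.97. The trial would have succeeded with an interval that does not exclude a near-doubling on the ratio scale.

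**6. What can happen at a low rate.** Take 9/459 (2.0%) vs 20/459 (4.4%). The difference is 2.40 points with standard error 1.15, so the 95% interval is 2.40 ± 1.96 × 1.15 = 0.14 to 4.65 points. The upper limit is below 4.7, so non-inferiority is declared, yet the interval excludes zero. The risk ratio is 2.22 (1.02 to 4.83). If the true rates were 2% vs 4%, this double result would occur about 12% of the time; at 3% vs 6%, about 0.3%.

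**The case against.** A fixed absolute margin is a common and legitimate choice, and the sample size is computed correctly for it. At the planned rate the test does its job: a true 6% vs 10.7% passes 2.7% of the time, and a doubling 0.4%. All of that stands.

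A reader might infer that any shortfall in bleeding lets a doubling through. The figures do not support that. At 5%, already below plan, a doubling is still outside the margin and passes 1.9% of the time. It becomes more likely than not to pass only below a 2.5% control rate.

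A reader might also infer that a low rate is to be expected, because Table 1 excludes several groups prone to bleed (age over 75, low haemoglobin, low platelets, poor renal function, low weight). The article points both ways. It enrols patients with gastritis, erosion or healed bleeding and ulcers, names previous gastrointestinal disease as a main risk factor for upper gastrointestinal bleeding, and describes higher bleeding risk in Asian patients. Above 6% the fixed margin is relatively stricter.

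A tempting remedy is to shrink the margin using the blinded pooled event rate. I do not recommend it. Such a margin is solved from power rather than from what excess is acceptable, and the harm itself widens it: at 2% vs 4% the pooled rate is 3% and the margin 2.996 × √(2 × 0.03 × 0.97 / 459) = 3.4 points, a ratio of 5.4 / 2 = 2.7. A doubling would still pass 22% of the time there.

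The DSMB, the separate BARC 3–5 endpoint and the per-protocol reanalysis help to bring harm to light, but none of them changes the success criterion or what it allows the trial to claim. Which effect measures are tabulated is often left to an analysis plan that is not shown. The point here is the stated rule set against the stated aim.

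**Conclusion.** The point holds in this form. At the planned 6% rate the margin allows up to a 78% relative excess (risk ratio 1.78), so non-inferiority alone cannot be reported as no increase in bleeding. That conclusion does not depend on the event rate being lower than planned.

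The risk of accepting a doubling is conditional. It is negligible at 5–6%, modest at 4% (7%), and material at 3% (26%) and 2% (67%). These figures assume 459 evaluable patients per arm and a Wald limit. The rates below 6% are illustrations, because the article reports none from the trial. The documents do not support saying that the trial is likely to pass a doubling, or that its sample size is wrong. Severity: should be fixed.

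**What to change.** Before unblinding, add a short paragraph to the analysis plan:

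- Keep the 4.7-point test at one-sided 0.025.
- Pre-specify the risk ratio with its 95% limits beside the risk difference for the primary endpoint.
- Word success as *excludes an excess of 4.7 points or more*, with the observed risk ratio and its upper limit stated, and not as no increase in bleeding.
- If the 95% interval for the difference lies wholly above zero, report significantly more bleeding on rivaroxaban alongside any non-inferiority statement.

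Do not replace the margin with one computed from the blinded pooled rate. The change needs no extra patients and leaves power and type 1 error as they are. The cost is a conclusion that sounds less favourable.
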